##### **d) Quality of Life Questionnaires:**

We will use the “Incontinence Quality of Life Questionnaire (I-QoL)” to assess quality of life. The I-QoL consists of 22 questions organized into three domains that assess behavioral limitations, psychosocial impact, and social embarrassment. All responses are assigned values ranging from 1 to 5, therefore allowing for quality of life to be measured on a scale from 0 to 100. The lower the score, the worse the quality of life. [35]

##### **e) Safety Assessment of Cell Therapy:**

Participants will have unrestricted access to the research center and investigators during and after the study, in order to maintain close safety monitoring. During postoperative follow-up visits, the presence of adverse effects will be assessed, such as: irritative symptoms (increased urinary frequency, dysuria, suprapubic pain, urgency, and urge incontinence); signs suggestive of urinary tract infection; obstructive symptoms (incomplete bladder emptying sensation, decreased urinary stream, need to strain during urination); infection or fluid collection at the puncture site; vulvovaginal itching or infection; hematuria. If a urinary tract infection (UTI) is suspected,

urinalysis and urine culture will be performed for diagnostic confirmation. If partial or total urinary obstruction is suspected, free uroflowmetry and post-void residual measurement via ultrasound will be performed. Partial obstruction will be defined as post-void residual > 150 ml; in such cases, expectant management with behavioral measures to aid bladder emptying will be adopted. In cases of total obstruction after periurethral injection, the patient will be managed with indwelling catheterization and weekly follow-up visits to assess her voiding pattern. The catheter will be removed when the post-void residual is < 150 ml.

We do not anticipate serious adverse effects from adult stem cell therapy, which has been proven not to carry a risk of tumor formation. Furthermore, previous studies on cell therapy for SUI have demonstrated the safety of this treatment. [16–18] As described in the following sections, appropriate methods for the identification and characterization of stem cells will be employed.

#### **f) Management of Study Step Failures:**

In cases where it is not possible to carry out the laboratory procedures, or the procedures for harvesting or injecting the stem cells due to technical difficulties or patient discomfort, the participant's involvement in the study will be discontinued. In the event of adverse effects, the patient will be promptly assisted by the research team and will have full access to the outpatient and hospital structure (Hospital São Paulo), if necessary.

### **4.6 Method of Preparation of BM-MSCs (Bone Marrow-Derived Mesenchymal Stem Cells)** **I – Isolation of Bone Marrow-Derived Stem Cells from Primary Culture of Bone Marrow Biopsy**

#### **Collection:**

Using appropriate sterile material and aseptic technique, and under local anesthesia with 2% lidocaine, bone marrow aspiration will be performed from the anterior and posterior iliac crests of the patients, depending on individual assessment. Approximately 50 ml of bone marrow solution will be collected.

#### **Processing and Cell Culture:**

All processing steps will be carried out under sterile conditions in a specific laminar flow hood. The bone marrow material will be cultured in Dulbecco's Modified Eagle Medium (DMEM). Using Ficoll-Paque, the solution will be centrifuged at 500 rpm for 30 minutes at 22°C. The cell layer at the Ficoll-solution interface will then be collected, resuspended in phosphate-buffered saline (PBS), and washed three times to remove any Ficoll residue. The cells will be suspended in DMEM supplemented with fetal bovine serum, penicillin, and streptomycin, and placed in an incubator for 24 hours to allow adherence to the plastic surface.

The DMEM solution with the resuspended cells will be distributed in 75 cm^2 culture flasks and maintained in a humidified incubator at 37°C with 5% CO2. Under sterile conditions, after 24 hours of isolation and cell adhesion to the culture flask, the medium will be removed by aspiration using a sterile fine-tipped Pasteur pipette. The flask will then be washed three times with PBS containing penicillin and streptomycin at 37°C, and fresh DMEM will be added. To maintain the culture, the medium will be renewed every 48 hours.

When the cells adhered to the flask reach approximately 80% confluence, they will be passaged through trypsinization. This procedure aims to detach the cells from the flask and transfer them to another vessel and/or use them in subsequent procedures (cells will be used between the second and third passages). For trypsinization, the culture medium will be removed by aspiration and the flask washed with PBS supplemented with 0.5M EDTA. After removing the PBS solution

by aspiration, a solution of 0.10% trypsin and 0.02% EDTA will be added in a volume equal to that of the previous medium, and incubated for 3 minutes. Trypsin will then be neutralized using DMEM. The resulting cell suspension will be centrifuged at 300 rpm for 6 minutes, the supernatant was removed by aspiration, and the cells were resuspended in DMEM. The cells were maintained in a humidified incubator at 37°C and 5% CO2 until they once again reached approximately 80% confluence.

## **II – Isolation of Myoblasts and Fibroblasts from Primary Culture of Muscle Biopsy**

**Collection:** Under local anesthesia, samples of the *quadriceps femoris muscle* (approximately 0.3 cm^3) will be collected by percutaneous needle biopsy and transported to the laboratory in transport medium containing 15 mL of 1X PBS with 10 µg/mL amphotericin B and 4% penicillin/streptomycin (10,000 IU, 10 mg/mL). The transport will be conducted in a thermal container with ice at a temperature of 4±2°C. Processing must occur within 24 hours of collection.

**Processing:** All processing steps will be performed under sterile conditions in a laminar flow hood. In summary, the tissue fragment will undergo enzymatic digestion using type II and IV collagenases to obtain the two cell types. The material will be centrifuged at 400g for 5 minutes, and the resulting cell pellet will be resuspended in the appropriate culture media.

**Cell Culture:** If cell expansion or increased yield is necessary, the cells will be cultured in flasks treated with Cellstart-CTSTM (Invitrogen). Fibroblasts will be cultured in DMEM:F12 medium with 20% fetal bovine serum (FBS), while myocytes will be cultured in a chemically defined MCDB 153 medium. Both media will be supplemented with 1% glutamine, 1% amphotericin B (250 µg/mL solution), and 1% penicillin/streptomycin (10,000 IU, 10 mg/mL). The cells will be either cryopreserved or used between the 3rd and 5th passages.

## **III – Isolation of Adipocytes from Primary Culture of Adipose Tissue Biopsy**

**Collection:** A lipoaspirate sample will be collected after asepsis and antisepsis, followed by infiltration of 50 cc of 0.25% lidocaine solution with epinephrine 1:500,000 into the abdominal wall region. The material will be aspirated using syringes equipped with 3 mm diameter cannulas. The samples will be immediately transferred to a sterile 100 mL culture flask containing 50 mL of Hank's Balanced Salt Solution (HBSS) supplemented with 100 U/mL penicillin and 100 µg/mL streptomycin.

**Processing:** In a sterile environment, under a laminar flow hood, the tissue fragments will be washed in six beakers containing 20 mL of HBSS solution using sterile forceps and the fragments will be transferred to a 100 mm^2 Petri dish, and the adipose tissue will be dissected and cut into small fragments of approximately 0.5 mm^3 using iris scissors. The resulting fragments will be transferred to a sterile 100 mL glass flask and incubated with type II collagenase (Sigma Chemical Company, St. Louis, MO, USA), at a concentration of 1 mg/mL in HBSS, using a ratio of 5 parts collagenase to 1 part tissue. The mixture will be agitated for 10 minutes at 37°C. The resulting solution will be filtered through a 250 µm nylon mesh. The filtrate will be transferred into sterile 50 mL conical tubes and centrifuged for 10 minutes at 300 g at room temperature.

**Cell Culture:** The pellet will be transferred to a 50 mL conical tube and washed with 20 mL of Dulbecco's Modified Eagle Medium (DMEM)/Ham's F-12 Nutrient Mixture (Sigma Chemical Company, St. Louis, MO, USA) supplemented with 10% fetal bovine serum (FBS), 0.1% bovine serum albumin (BSA), and 100 U/mL of penicillin and streptomycin.

#### **IV – Characterization, Quality Control, and Biosafety of Cell Populations**

To ensure the quality of the samples and cultured cells, the following will be performed: flow cytometry for immunophenotyping and cell cycle analysis, as well as differentiation assays (osteogenic, chondrogenic, and adipogenic) to characterize stem cells. For biosafety control of the cultures, karyotyping and both aerobic and anaerobic blood cultures will be performed.

The cell populations obtained from each patient's samples will be characterized using the following markers: CD29, CD44, CD73, CD90, CD105, CD166, CD146, CD14, CD19, CD45, HLA-DR, CD34, CD11B, CD31, CD106, CD4, CD5, CD9, CD10, CD13, CD36, CD38, CD45, CD49, CD56, CD133, STRO-1, OCT4, SOX-2, Nanog, SSEA-4, HLA-ABC, HLA-DR, CXCR-4, LIN, MHC-I, MHC-II, vimentin, smooth muscle actin, Flk-1, Sca-1, BCL, and vWf.

#### **4.7 Logistics, Physical and Laboratory Infrastructure, Biorepository**

At UNIFESP, the participants will undergo clinical evaluations and pre-treatment testing. Subsequently, they will be referred to the Hematology and Hemotherapy Department at HIAE, where bone marrow biopsies and peripheral blood collection will be performed. The extraction and cultivation of stem cells will be conducted in the human cell therapy laboratory within the Hematology and Hemotherapy Department at HIAE. At the time of treatment, the injection of autologous stem cells will be carried out at the Urogynecology Department of UNIFESP.

Similarly, the skeletal muscle and adipose tissue biopsies obtained at UNIFESP (Hospital São Paulo) will be sent to the Stemcorp cell therapy laboratory for stem cell isolation and cultivation.

The transport of biological material between research centers will comply with Anvisa (Brazilian Health Regulatory Agency) regulations, ensuring proper packaging of the samples.

This research involves the creation of a biorepository located at HIAE and at Stemcorp, specifically tied to this project. The biorepository will be deactivated upon the completion of the study. Biological products derived from these samples during and after the study will be incinerated in accordance with biospecimen disposal regulations.

#### **4.8 Database**

The participants' identification, along with their clinical, epidemiological, and diagnostic test data, will be assigned sequential codes. This information will be compiled in a virtual database accessible to the research centers, where laboratory analysis results will also be added. These data will also be stored in a repository at UNIFESP, with access and updates managed by the primary research center.

#### **4.9 Periurethral Injection of the Cell Preparation**

Transparent syringes will contain 5 mL of solution (stem cells + human serum) to be injected into the mid-urethral region, at the level of the urethral sphincter. Under urethrosopic guidance, a needle will be introduced through the device to the appropriate location and inserted approximately 3 mm into the mucosa. A total of 2.5 mL will be injected at the 3 o'clock position and 2.5 mL at the 9 o'clock position, without urethral obstruction. The procedure will be performed on an outpatient basis, and there will be no need for anesthesia or analgesia.

#### **5. Post-Procedure Evaluation**

The patient will be observed for two hours following the procedure. Follow-up visits will occur at 7, 30, 60, and 180 days for clinical evaluation after treatment.

One year after the procedure, patients will complete another round of questionnaires, pad test, and cystometry with leak point pressure evaluation. These data will be disclosed only after the final assessment of the entire study population.

The **primary outcome** is improvement in quality of life, which will be assessed using the I-QoL questionnaire before and after treatment. Patients scoring between 0 (complete cure) and 20 (inclusive) on the post-treatment I-QoL will be considered improved. Patients with scores above 20 will be considered not improved.

In addition, patients will be considered cured if they show no signs of urinary leakage during the clinical examination, cystometry, or pad test.

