## **4. Methodology**

### **4.1 Study Design and Population:**

Prospective randomized clinical study involving 45 patients with SUI who will receive peri-urethral injection of 5 ml solution containing 100 million autologous ASCs (derived from muscle, bone marrow, or adipose tissue).

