## 6. Statistical Method

**Data processing and analysis:** The SAS software version 8.2 will be used to verify data consistency and perform statistical analysis.

**Descriptive analysis:** Descriptive analysis will be used to characterize the study sample. For categorical variables, absolute and relative frequency distributions will be used. For continuous variables, measures of central tendency (mean and median) and variability (standard deviation, upper and lower limits) will be applied.

**Inferential analysis:** Comparisons between pre- and post-treatment parameters will be analyzed using the *Wilcoxon rank-sum test* and *Student's t-test* for non-parametric and parametric variables, respectively. The *Chi-square test* and *Fisher's exact test* will be used to assess the homogeneity of categorical variables (race, hormonal status, and previous surgeries for stress urinary incontinence), as well as the absence of urinary leakage on urodynamic testing after the intervention. The *Mann-Whitney test* will be applied to assess the homogeneity and possible differences in medians of continuous variables between pre- and post-treatment groups that measure treatment success measured by the "I-QoL" questionnaire and pad test) will be assessed. For all statistical tests, a significance level of 0.05 or 5% ( $\alpha \leq 0.05$ ) will be adopted as the threshold for rejecting the null hypothesis.

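### Sections 4.5 d) and 5 of the protocol give the I-QoL opposite directions, so the primary-outcome rule for improvement is inverted on the only scale the protocol describes

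*Protocol*

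**What the plan says.** Section 4.5 d) is the protocol's only description of the questionnaire. On structure it says: "The I-QoL consists of 22 questions organized into three domains". Each item takes a value from 1 to 5, and the total is expressed on a range whose lower end is 0 and whose upper end is 100. On direction it says: "The lower the score, the worse the quality of life". Hence 0 is the worst score and 100 the best.

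Section 5 defines the primary outcome, which "is improvement in quality of life, which will be assessed using the I-QoL questionnaire before and after treatment". The questionnaire is repeated one year after the procedure. The classification rule is: "Patients scoring between 0 (complete cure) and 20 (inclusive) on the post-treatment I-QoL will be considered improved", followed by: "Patients with scores above 20 will be considered not improved".

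Section 6 lists the I-QoL among the continuous measures to be compared before and after treatment. The categorical tests it names are assigned to race, hormonal status, previous incontinence surgery and absence of leakage on urodynamic testing. The improved/not improved classification is not among them.

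**The concern.** The two sections name the same instrument and give it opposite directions. In section 4.5 d) a score of 0 is the worst possible quality of life; in section 5 it is a complete cure. Section 5 is also consistent within itself: the label on 0, the band for improved and the band for not improved all treat low scores as good. A single mistyped number would not explain that.

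At stake is the only success criterion that section 5 gives for the primary outcome. If the instrument is scored as section 4.5 d) describes and the rule is applied as section 5 states, the reported improvement rate falls when quality of life gets better and rises when it gets worse. If someone notices at the analysis stage, the direction and the cut-off would have to be chosen then, possibly with the data in view.

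**Working it through.** **Inputs**, all from the protocol: 22 items, each scored 1 to 5, total expressed on 0 to 100, lower is worse (section 4.5 d); improved is 0 to 20 inclusive, not improved is above 20 (section 5). The rescaling formula is not given. I assume the usual linear one:

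score = (item sum − 22) / 88 × 100, where 88 = 22 × 5 − 22.

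**Reproducing the stated range.** All items at 1: (22 − 22)/88 × 100 = 0. All items at 5: (110 − 22)/88 × 100 = 100. This matches the 0 to 100 in section 4.5 d).

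**Where the cut-off falls.** A score of 20 corresponds to an item sum of 22 + 0.20 × 88 = 39.6, a mean item value of 39.6/22 = 1.8. Item sums are whole numbers when all items are answered, so:

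- sum 39: (39 − 22)/88 × 100 = 19.3, improved;
- sum 40: (40 − 22)/88 × 100 = 20.5, not improved.

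Improved therefore means sums of 22 to 39 and not improved means sums of 40 to 110.

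**The rule on the scale of section 4.5 d)**

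| I-QoL before | I-QoL at one year | Change in quality of life | Class under section 5 |
|---|---|---|---|
| 30 | 100 | better, to the best possible score | not improved |
| 30 | 10 | worse | improved |

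The examples are invented scores, but any scores on the same sides of 20 give the same classes.

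**Direction of the improvement rate.** The rate is the proportion with a score of 20 or less. If scores shift upwards, women can only leave that group, so the proportion falls or stays the same. This needs no assumption about the distribution and does not depend on the rescaling formula, the 45 patients or the 5% significance level.

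**The comparison in section 6.** It uses the I-QoL scores themselves and not the cut-off of 20, so its computed result is the same whichever section is right. If scores rise, it shows a rise while the improvement rate falls or stays flat. Which of these counts as benefit cannot be read until the direction is settled.

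**The case against.** The strongest objection is that section 4.5 d) may hold the mistake. If the questionnaire is in fact scored with 0 as the best value, the rule in section 5 is coherent and only the sentence on direction needs correcting. The documents cannot exclude this. The protocol makes two statements of direction and has no third to decide between them: the inclusion criterion in section 4.3 uses the I-QoL but gives no threshold. A reader might infer that section 5 is shown to be the wrong one. The documents do not support that; they show a conflict, and the inversion follows only on the scale as section 4.5 d) describes it. The conflict remains either way.

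A reader might also infer that the trial's main result will carry the wrong sign. That goes too far. Section 6 names no test for the improved/not improved classification and plans a comparison of I-QoL scores that does not use the cut-off. The damage is to the responder classification, and to its agreement with that comparison.

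A third inference would be that a woman at or below 20 has given nearly the worst answer to every item. The value 1.8 is a mean. A sum of 39 also arises from four items at 5, one at 2 and seventeen at 1 (20 + 2 + 17 = 39).

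Finally, a statistical analysis plan may exist and might state a scoring direction. That would not remove the contradiction, because the protocol itself fixes both directions explicitly.

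**Conclusion.** The contradiction is certain and needs no outside source: the primary-outcome rule cannot be applied consistently as written. On the protocol's only description of the scale, the rule is fully inverted. The lowest fifth of the range (0 to 20 of 100) is success, and everything above it, including the best possible score, is failure.

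That consequence is conditional on section 4.5 d) being correct. The item sums also assume linear rescaling. I give no expected percentage of women misclassified, because the protocol states no I-QoL mean or standard deviation from which to derive one.

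This must be fixed before the primary outcome is analysed.

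**What to change.** Reconcile sections 4.5 d) and 5 so that one direction holds throughout.

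- **If section 4.5 d) is right:** remove the cure label on 0 and the 0 to 20 band from section 5. Replace them with a criterion on the higher-is-better scale, given as a cut-off or as a change from baseline, and state that a positive 12-month minus baseline difference is benefit. Deleting the band alone is not enough, since improvement would then have no definition.
- **If the 0 to 20 rule was written for a reversed score or another instrument:** correct section 4.5 d), with the scoring and direction actually used.

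The intended cut-off should come from the sponsor. The mirror image of 0 to 20 would be 80 to 100 (item sum at least 22 + 0.80 × 88 = 92.4, mean item at least 4.2), but the protocol nowhere states it and it should not be assumed. The present rule also looks only at the post-treatment score, although the outcome is described as assessed before and after treatment, so the sponsor should say whether change from baseline is meant.

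Direction and cut-off must both be fixed before any analysis of the primary outcome. The cost is a protocol amendment to the primary-outcome definition, with no new data or patients.

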### **4.3 Participants**

#### **Inclusion Criteria**

1. Patients with moderate stress urinary incontinence (SUI), primary and refractory to previous clinical treatments (behavioral therapy and physiotherapy), confirmed by physical examination (stress test), I-QOL questionnaire, cystometry (urodynamic study), and pad test (between 10 and 50 grams).

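### The primary outcome is improvement in I-QoL, but women are classed on the post-treatment score alone, and section 6 analyses a different quantity

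*Protocol*

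**What the plan says.** Section 5 (Post-Procedure Evaluation) states that the primary outcome "is improvement in quality of life, which will be assessed using the I-QoL questionnaire before and after treatment". The rule that follows is: "Patients scoring between 0 (complete cure) and 20 (inclusive) on the post-treatment I-QoL will be considered improved". The complement is: "Patients with scores above 20 will be considered not improved".

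Section 4.3 (Inclusion Criteria) requires moderate SUI "confirmed by physical examination (stress test), I-QOL questionnaire, cystometry (urodynamic study), and pad test (between 10 and 50 grams"). Of these tests only the pad test has a numeric range.

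Section 4.5 d) describes the I-QoL as 22 items scored 1 to 5, rescaled to 0–100, and adds: "The lower the score, the worse the quality of life". Section 5 runs the other way, since it labels 0 as complete cure.

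Section 6 (Statistical Method) assigns the Wilcoxon rank-sum test or Student's t-test to pre/post comparisons. It assigns the Mann-Whitney test to medians of continuous variables, pre against post, in a sentence that refers to "treatment success measured by the 'I-QoL' questionnaire and pad test". Chi-square and Fisher's exact tests go to race, hormonal status, previous SUI surgery and absence of leakage on urodynamics. Improved/not improved is not on that list.

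**The concern.** Improvement is a statement about change. A rule that looks only at the final score describes where a woman ended, and that depends on where she started as well as on what happened to her. Two kinds of error follow. A woman already inside the cut-off at entry can be counted as a success with no change or after a decline. A woman with a large gain that stops short of the cut-off is counted as a failure.

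The protocol also leaves open which result is the primary one. Section 5 defines a yes/no classification, while section 6 fixes a comparison of continuous scores. These can point in different directions. With both available, the choice of which to report as primary could be made after the 12-month data are seen.

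**Working it through.** The protocol states no effect size, SD or responder rate for I-QoL, so there is no figure of its own to reproduce. The check has three parts.

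**1. The rule applied to individual scores.** In section 5's direction (0 best), improved means post ≤ 20, whatever the baseline.

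| Baseline → 12 months | Change | Classed as |
|---|---|---|
| 20 → 20 | none | improved |
| 10 → 20 | 10 points worse | improved |
| 90 → 21 | 90 − 21 = 69 points better | not improved |

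No entry limit on I-QoL rules out the first two rows.

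Now correct the direction to that of section 4.5 d) by replacing each score x with 100 − x. The rule becomes post ≥ 80, and the rows become 80 → 80 (improved), 90 → 80 (10 points worse, improved) and 10 → 79 (69 points better, not improved). The fault is therefore separate from the direction error. This part needs no assumption beyond the protocol's text.

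**2. Endpoint against analysis.** Section 5 defines a binary variable. The I-QoL analysis in section 6 is of a continuous variable, pre against post. The categorical tests in section 6 are given a list of variables that omits the binary one. The general sentence on frequencies for categorical variables could tabulate it, but that sentence is there to characterise the sample.

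**3. How much it could matter.** All inputs here are assumptions, since the protocol gives none:

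- baseline ~ N(m, s²), with m from 30 to 60 and s from 15 to 25
- 12-month score ~ N(m + 20, s²), with correlation r from 0.3 to 0.7
- scores clipped to 0–100; 400,000 simulated women per setting
- cut-off mirrored to 80, on the scale of section 4.5 d)

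Two shares were computed:

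- A = P(post < 80 given gain ≥ 20): large gains classed not improved
- B = P(gain < 10 given post ≥ 80): women classed improved with little gain

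| Setting | A | B |
|---|---|---|
| m = 45, s = 20, r = 0.5 | 66% | 11% |
| Lowest over the grid | 30% | 1% |
| Highest over the grid | 96% | 29% |

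In the m = 45 setting, excluding out-of-range scores instead of clipping them gives A = 69% and B = 11%. In that setting 3–4% of women already meet the cut-off at baseline, and about 3% of those classed improved have no gain at all.

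**The case against.** Several objections deserve an answer.

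- **Women counted as improved without any gain may be few.** This stands for the middle setting: about 3% of the improved, which is under 1% of all women treated. Entry also requires SUI confirmed by the I-QoL, which makes near-normal baselines less likely, although no number enforces that. In that setting the commoner error is the large gain classed as failure.
- **Any single misclassification figure rests on invented inputs.** This stands. The cut-off of 80 is itself a construction, and raising the 12-month mean or lowering the cut-off reduces share A considerably. Only a range should be quoted.
- **The cut-off might be a supplementary label**, like the definition of cured in the next paragraph, with the continuous pre/post comparison as the true primary analysis. The section 6 sentence is also visibly damaged, and test details may sit in an SAP. This does not rescue the text. The cut-off stands in the primary-outcome paragraph and is what defines improved there. The mismatch is between two things the protocol itself fixes, so it is not a detail left for later.
- **An end-state responder definition is a legitimate type of endpoint.** That is true if it is named as such. It is not a measure of improvement before and after treatment.

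A reader might also infer that dichotomising costs the trial much of its power to compare the three cell sources. The protocol does not support that. Section 6 names no I-QoL comparison between cell sources, section 4.1 gives 45 patients without an allocation ratio, and the I-QoL analysis that is named is continuous.

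**Conclusion.** The point holds. The rule for improved ignores baseline, no entry limit repairs this, and the variable it creates is not the one section 6 analyses. Those conclusions rest on the text alone and survive correction of the scale direction.

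The size does not rest on the text. Under the stated assumptions, about 30–96% of women gaining at least 20 points would be classed not improved, and about 1–29% of the improved would have gained under 10 points. These ranges show that the misclassification can be large; they do not predict this trial's result. It would go too far to say that many women will be called improved with no change, or that the planned I-QoL analysis loses information or power through the cut-off.

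Because this is the primary outcome, it should be corrected before any 12-month data are seen.

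**What to change.** In section 5, make the primary endpoint each woman's change in total I-QoL score from baseline to 12 months, in the direction given in section 4.5 d). In section 6, name a paired analysis of that same variable.

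If a responder rate is kept, make it secondary. Define it as a minimum gain from the woman's own baseline, with the number of points and its source written in before any 12-month data are seen. Assign it its own analysis.

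The cost is protocol wording only. Both I-QoL measurements are already planned ("which will be assessed using the I-QoL questionnaire before and after treatment"), so no visit, test or patient is added.
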